### Sample size calculation

Approximately 580 participants (290 per group) will be recruited. The study will have 80% power to detect as significant at the 5% level a 23% reduction in the rate of falling (i.e. an IRR of 0.77 using negative binomial regression analysis) in the 13-month follow-up period. This represents a reduction from 0.85 falls/person (an established rate of falling in a high-risk control group equivalent to our sample) [22,23] to 0.65 falls/person in the intervention group. This allows for an 8% loss to follow-up defined as withdrawing from the study and/or not completing the falls diaries, 70% compliance in the intervention participants and a rate of 0.57 falls/person among those complying with the intervention

### Statistical analysis

The primary analysis will be by intention to treat. The number of falls per person-year will be analysed using negative binomial regression to estimate the difference in falls rates between the two groups, adjusted for confounding variables if required. This analysis takes into account all falls during the trial, and the distribution of falls, which is Poisson-like but containing a wider, higher tail in the distribution [24]. Three *a priori *subgroup analyses will be performed using a test for statistical interaction to assess whether the intervention effect size differs according to: (i) baseline physiological falls risk [18]; (ii) number of participant-reported falls in the year prior to the trial; and (iii) participant-reported outdoor activity levels during the trial as assessed with the AAP [14]. Secondary analyses will assess the effects of the intervention on falls that occur (i) within and (ii) beyond the participants' homes. Longitudinal mixed models will be used to assess the effect of group allocation on the continuously-scored secondary outcome measures. Predictors of adherence will be established using multivariate modelling techniques. Analyses will be conducted using the SPSS [25] and Stata [26] computer programs.

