### Initial Assessment

Initially the study aims will be explained, and then the participants will be asked if they feel confident that they could manage and wear two pairs of glasses if randomised to the intervention. Only participants who answer 'very or quite confident', as opposed to 'not confident' or 'very unconfident', will undergo consent, assessments and randomisation. The approach of targeting the intervention to those who consider it to be reasonable and manageable is based on strong evidence from hip protector trials [13].

Demographic details and potential confounders will be recorded, including age, gender, living alone status, MMSE [10], number of falls in past year, number and type of medications, physical activity levels, gait aids, medical conditions relevant to falls (e.g. arthritis, syncope, diabetes and depression), current glasses use and ocular history. Baseline lifestyle activities (using the Adelaide Activities Profile (AAP)) [14], health status (SF-12) [15], and falls efficacy (Falls Efficacy Scale – International (FES-I scale) [16] will be measured.

The following vision and physical assessments will then be carried out. Corrected and uncorrected uniocular and binocular visual acuity will be assessed using a 3-metre logMAR chart [17]. Falls risk will be measured with the short-form Physiological Profile Assessment (PPA) [18] which includes five validated measures of physiological falls risk (visual contrast sensitivity, postural sway, quadriceps strength, reaction time and lower limb proprioception). In multivariate models these variables provide an overall falls risk score, and can predict those at risk of falling with 75% accuracy in community and retirement village settings. Functional mobility will be assessed with the TUG test [10], and the sit-to-stand test [19].

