### Randomisation

After completion of the initial assessment, participants will be formally entered into the study and randomised to intervention or control groups. Participants will be stratified by assessment site (Greenwich or Prince of Wales Hospitals) and recruitment source (hospital or community contact).

Then each stratum will be randomly allocated in permuted blocks of 10 using sequentially-numbered opaque envelopes containing group assignment.

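### The primary falls model is adjusted only "if required", with no criterion and no statement of which rate ratio is primary; fix one covariate-adjusted model in advance

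*Protocol article*

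**What the plan says.** All references are to the protocol article.

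- **Statistical analysis.** "The primary analysis will be by intention to treat". The number of falls per person-year is compared between groups by negative binomial regression, "adjusted for confounding variables if required". No variables, trigger or time of decision are given, and neither the adjusted nor the unadjusted IRR is named as the primary result. The same section does name baseline physiological falls risk and prior-year falls in advance, but as subgroup variables.
- **Randomisation.** Allocation follows the initial assessment and is stratified by assessment site (two hospitals) and recruitment source (hospital or community), which makes four strata; "each stratum will be randomly allocated in permuted blocks of 10". The Statistical analysis section neither includes nor excludes these factors.
- **Initial Assessment.** "Demographic details and potential confounders will be recorded, including age, gender, living alone status, MMSE [10], number of falls in past year", followed by medications, activity, gait aids, medical conditions, glasses use and ocular history. The Physiological Profile Assessment (PPA) is also measured, and its component variables are said to give a risk score that "can predict those at risk of falling with 75% accuracy in community and retirement village settings".

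**The concern.** Many different models satisfy the same sentence: no covariates, any one item from the baseline list, or several of them. The text does not settle which of these yields the headline IRR and p-value.

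The stated reason for adjusting is also unsuitable. Confounding is a problem of non-randomised comparisons. Here treatment is allocated by permuted blocks, so a baseline difference between the groups is chance. The case for adjusting is that a covariate predicts falls, and that can be judged before any data are seen.

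Two things are at stake. One is credibility: nothing in the wording stops the choice of model from being made with the results in view. The other is precision: prior-year falls and the PPA score will improve the estimate only if someone later decides that adjustment was needed.

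**Working it through.** The plan attaches no figure to the adjustment rule, so there is none to reproduce. The checks below ask what the rule could cost.

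**Inputs from the protocol article:** 290 per group, 0.85 versus 0.65 falls per person, 8% loss, 5% level (Sample size calculation). Analysed per group: 0.92 × 290 = 266.8, about 267, or about 534 in all.

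**Inputs assumed, because the article does not give them:** a two-sided test, the dispersion k, the strength of the covariates, and the correlation r between adjusted and unadjusted test statistics.

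**1. Type I error if the better of two tests is reported.** Error = 1 − P(|Z₁| < 1.96 and |Z₂| < 1.96), with Z₁ and Z₂ standard normal and correlation r.

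| r | error |
|---|---|
| 0.95 | 6.5% |
| 0.97 | 6.1% |
| 0.985 | 5.8% |

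With eight candidate models (unadjusted, all six covariates, each covariate alone), a simulation of 2,000 trials at k = 0.7 gave 8.4% for the smallest p-value.

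**2. Type I error if adjustment depends only on baseline imbalance.** Write the unadjusted statistic as Zᵤ = r·Zₐ + √(1 − r²)·D, where Zₐ is the adjusted statistic and D the standardised imbalance, independent of Zₐ under the null. Use Zₐ when |D| > 1.96 and Zᵤ otherwise. The error is 4.7%, 4.8% and 4.9% for r = 0.95, 0.97 and 0.985. The simulation in step 1 gave 4.7% for this rule, against 5.0% for the unadjusted model and 5.0% for the prespecified adjusted model. The rule does not inflate error, because it uses the unadjusted statistic only when D is small.

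**3. Precision from prior-year falls alone.** Simulated negative binomial fits with 267 per group, dispersion about 1, and 50% to 80% of the log-frailty variance shared between years:
- standard error of the log IRR 0.128 to 0.126: (0.126/0.128)² = 0.97
- standard error 0.129 to 0.123: (0.123/0.129)² = 0.91 from the rounded values (0.90 unrounded)

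The variance falls by about 3% to 10%. As a share of 580 participants this is 0.03 × 580 ≈ 17 to 0.10 × 580 = 58.

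**4. Power with prespecified prognostic covariates.** SE² = (1/0.85 + 1/0.65 + 2k)/266.8 = (2.715 + 2k)/266.8; power = Φ(|ln(0.65/0.85)|/SE − 1.96), with |ln(0.65/0.85)| = 0.268. Covariates that explain a share of the dispersion reduce k by that share.

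| k | share explained | power by formula | power by simulation |
|---|---|---|---|
| 0.5 | 20% | 62.3% → 64.7% | 64.7% → 67.5% |
| 0.7 | 30% | not computed | 58.3% → 62.9% |
| 1.0 | 30% | 52.3% → 57.9% | 50.3% → 57.2% |

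The simulations used 600 to 1,000 runs, so each power has a Monte Carlo standard error of up to about 2 points. The gain is roughly 2 to 7 points.

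**5. The strata.** Simulation with 540 analysed, k = 0.7, blocks of 10 within four strata, and an effect given to recruitment source only (2,000 runs; Monte Carlo standard error of the null rates about 0.5 points):
- hospital and community rates differing 1.5-fold: including source changes power by under 1 point
- differing 2-fold: power 56.7% without source, 59.4% with it; type I error 4.2% without, 5.0% with

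Omission therefore costs about 0 to 3 points of power and makes the test slightly conservative. Blocking keeps the groups balanced within strata, so omission does not bias the IRR.

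**The case against.** The strongest reply is that this is a condensed journal article. Covariate lists commonly go into the full protocol or analysis plan, which are not shown, so their absence is no fault. That is right about the list, and it disposes of any complaint that the strata or particular covariates are missing. It does not dispose of the sentence itself. The article is not silent on adjustment; it sets a conditional rule. An analysis plan with a fixed model would have to override that rule, and one that followed it would inherit the ambiguity.

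Several stronger readings are tempting, and the article does not support them:

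- **That adjustment is triggered by observed imbalance.** No trigger is stated. If it were imbalance, error would stay near 5% (step 2).
- **That the type I error is inflated.** The 5.8% to 6.5% (and 8.4% for eight models) arises only if the model is picked by its result. The wording neither prescribes this nor prevents it.
- **That the primary model omits the strata.** The text does not say so, and the consequence would be small.
- **That precision is discarded.** Adjustment is permitted, so precision is left to chance.

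The objection also stands on the size of the gain. Dispersion and covariate strength are assumed. Participants aged 65 to 79 may qualify through a fall in the past year, which could narrow the range of that covariate and weaken it as a predictor. Whether 580 is enough under overdispersion is a separate question and adds no weight here.

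**Conclusion.** The point holds in a limited form. The article makes adjustment of its primary model conditional, gives no criterion, bases it on confounding, and does not say which IRR is primary. The sentence should be changed. It is not evidence that the planned test is invalid or that its error rate exceeds 5%.

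The size is modest. The exposure is up to about 1.5 percentage points of type I error if the better of two tests were reported (assumed correlation 0.95 to 0.985), and essentially none under a pure imbalance rule. The forgone benefit is about 3% to 10% of the variance of the log IRR from prior-year falls alone, or a few points of power under dispersion 0.5 to 1 and covariates explaining 20% to 30% of it. None of these assumed values comes from the article.

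**What to change.** Replace the conditional phrase with one primary model, fitted whatever the observed balance: negative binomial regression with a log person-time offset and terms for group, assessment site, recruitment source and a short named list of pre-randomisation predictors of falls. Prior-year falls, PPA score and age are reasonable examples; other short lists are defensible if fixed, with their functional form, before outcome data are examined. State that the IRR from this model is the primary result and that the unadjusted IRR is supportive.

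The offset is already implied by analysing falls per person-year. All the variables are known before randomisation, so no new data are needed. The cost is a sentence or two and a few degrees of freedom among about 530 analysed participants.

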To date, there is no evidence that falls can be prevented by restricting the use of multifocal glasses. To address this need we are conducting the Visual Intervention Strategy Incorporating Bifocal & Long-distance Eyewear (VISIBLE) study. The primary aim of this randomized controlled trial is to determine whether the provision of supplementary single-lens distance glasses to elderly multifocal glasses wearers, together with recommendations for wearing them for standing and outdoor activities, can reduce falling rates over a 13-month period. Secondary aims include determining whether, as a result of fewer falls, the intervention has beneficial effects for physical and emotional wellbeing, falls efficacy and activity levels, and whether a range of physical, psychological and socio-demographic factors can predict compliance in the intervention group.

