#### Secondary outcome measures

Secondary outcome measures will include physical activity levels, falls efficacy and quality of life assessed at baseline and 12 months. These measures are included to determine whether, as a result of fewer falls, the intervention has beneficial effects on an older person's abilities and quality of life. *Physical activity levels *will be assessed with the Adelaide Activities Profile, a validated scale which measures lifestyle activities using 21 items which generate four domains (domestic chores, household maintenance, service to others, and social activities) [14]. Physical and emotional wellbeing will be assessed using the *SF 12 Version 2 *composite physical and mental scores [15]. Falls efficacy will be assessed using the *FES-I *[16] in which level of concern about falling when carrying out 16 activities is rated on a 4-point scale.

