## Discussion

Falls are the leading cause of injury-related death and hospitalisation in older persons [26]. Falls can also result in disability, restriction of activity and fear of falling – all of which reduce quality of life and independence [27,28]. Furthermore, falls can contribute to the placement of an older person into institutional care [28]. There is mounting evidence that multifocal glasses impair vision, hinder obstacle avoidance and increase the risk of falls in older people.

There are over 2.4 million people over 65 years of age in Australia, one-third of whom fall annually at least once [27]. Given that 52% of older people rely solely on multifocal glasses [1] and only 1% use separate reading and distance glasses [1], over one million Australians could potentially benefit from this trial immediately. Current guidelines recognise the importance of vision in falls and recommend that older people not walk while wearing multifocal glasses [29,30]. It is worth noting, however, that this recommendation also removes the correction of distance refractive error which may increase falls risk in some people. Our intervention, which involves providing multifocal glasses wearers with an additional pair of single-lens distance glasses for high-risk situations that increase postural threats (such as walking on stairs and in unfamiliar outdoor settings), will avoid this problem.

Thus, this program is optimally designed to address the major problem of falls in older people and could be readily translated into clinical practice. The study we are undertaking is designed and adequately powered to assess the effect of the program. There will be far-reaching benefits for older people, their carers and the community if this program can be demonstrated to assist in reducing the number of falls in this high-risk population.

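### Subgroup (iii) tests effect modification by outdoor activity during the trial, a post-randomisation measure, so its interaction test does not rest on the randomised comparison; baseline activity should be used instead

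*Protocol article*

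**What the plan says.** The Statistical analysis section plans three subgroup analyses, "using a test for statistical interaction to assess whether the intervention effect size differs according to" three factors. The first two are "i) baseline physiological falls risk [18]; (ii) number of participant-reported falls in the year prior to the trial". The third is "iii) participant-reported outdoor activity levels during the trial as assessed with the AAP".

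Four other places bear on the third factor:

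- **Secondary outcome measures:** "Secondary outcome measures will include physical activity levels, falls efficacy and quality of life assessed at baseline and 12 months". Physical activity "will be assessed with the Adelaide Activities Profile, a validated scale which measures lifestyle activities using 21 items".
- **Background:** a secondary aim is to find out whether, "as a result of fewer falls, the intervention has beneficial effects for physical and emotional wellbeing, falls efficacy and activity levels".
- **Discussion:** "Falls can also result in disability, restriction of activity and fear of falling".
- **Initial Assessment:** "Baseline lifestyle activities (using the Adelaide Activities Profile (AAP") are recorded, with randomisation following once this assessment is complete.

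**The concern.** A test of effect modification asks whether the treatment effect differs between kinds of people who could be told apart before treatment. Within levels of a baseline variable, randomisation still makes the arms comparable. Within levels of a variable measured after randomisation it need not, because treatment, or the outcome itself, may have decided who falls into which level.

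Subgroup (iii) is exposed on both counts. Activity may be altered by the intervention and can be reduced by falls, which are the primary outcome. People classed as less active at 12 months will include some who became less active because they fell. If the arms differ in how people reach that class, the subgroup rate ratios mix the treatment effect with differences in composition. An apparent interaction can then arise where there is none, or both ratios can shift together. Naming the analysis in advance does not remove this.

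At stake is one of three pre-specified subgroup results. It is close to the trial's rationale, since the glasses are meant above all for walking outdoors.

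**Working it through.** **Timing.** The AAP has two stated time points, baseline and 12 months. Only the second is after randomisation, so it is what the wording of (iii) refers to. Falls are counted over 13 months from randomisation. If the 12 months run from the same point, 12/13 = 92% of the counting window has passed when the AAP is taken.

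**Role.** The same section plans mixed models for the effect of allocation on the continuous secondary outcomes, which include the AAP. AAP activity is thus a response to allocation in one analysis and a classifier of participants in another.

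**Illustration of size.** The plan gives no figure to reproduce here, so the size can only be simulated.

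Inputs from the Sample size calculation section:
- 290 per group and 8% loss: 290 × 0.92 = 266.8, so 267 per arm.
- Control rate 0.85 falls per person and a rate ratio of 0.77 (0.65/0.85 = 0.765).

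Assumptions, not in the documents: the negative binomial dispersion k, every effect on activity, and the median split.

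Model, with T = 1 for intervention and no true effect modification:
- Falls: Y ~ Poisson(0.85 × 0.77^T × u), with u gamma, mean 1, variance k (0.5 or 1).
- 12-month activity: A1 = 0.7·A0 + b·Y + g·T + 0.7·e, with A0 and e standard normal. Here b is the change per fall and g a direct effect of the intervention, both in SDs of baseline activity.
- Test: z = (log IRR_high − log IRR_low)/SE, rejecting if |z| > 1.96; 2,000 runs per scenario. At a true rate of 5% the Monte Carlo error is √(0.05 × 0.95/2000) = 0.5 percentage points.

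| Split on 12-month activity | False interactions | IRR, less active | IRR, more active |
|---|---|---|---|
| Falls only, b = −0.3 in both arms | 5.5–6.6% | 0.77 | 0.79–0.81 |
| Uniform direct effect, g = ±0.3, b = −0.2 or −0.5 | near 5% | 0.72–0.90 (both subgroups) | 0.72–0.90 (both subgroups) |
| b = −0.3 control, −0.15 intervention | 28–35% | 0.68–0.70 | 0.97–1.04 |

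Larger gaps between arms in b give still higher rates: 69–74% for −0.5 against −0.2, and 77–86% for −0.3 against 0. With a true rate ratio of 1.00, the third row still rejects in about 29% of trials.

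A second model (k = 1, negative binomial regression with robust standard errors, 500 to 1,200 runs per scenario) makes frail people less active by 0.8 SD, lowers activity by 0.2 SD per fall, and lets the intervention change activity in frail people only:
- No direct effect: about 6%, subgroup ratios 0.78 to 0.82.
- +0.2 SD: 7%.
- −0.5 SD: 11%.
- +0.5 SD: 19 to 22%, with subgroup ratios of 0.75 and 1.04 in the 22% run.
- +0.8 SD: 40 to 42%.

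**Same data, split on baseline activity.** False interactions were 4.2 to 5.9% and the subgroup ratios 0.76 to 0.77 in the scenarios with a true ratio of 0.77.

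The pattern has a simple reason. If falls lower activity equally in both arms and nothing else does, selection into the less active class works almost alike in each arm and largely cancels. Once the arms differ in how activity responds, it does not cancel.

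**The case against.** The strongest reply is that the only route from intervention to activity that the article describes runs through fewer falls, and by that route alone the test is nearly sound: about 6% error and modest drift in the ratios. The rates of 20% and above need a direct effect confined to frail people, or a different effect of falls on activity by arm, and the article states neither. The median split is also assumed. With activity as a continuous moderator the rate at +0.5 SD fell from 19% to 15%, and falls-only stayed near 5 to 6%. All of this stands, and it limits what can be claimed about size. It does not make the comparison a randomised one.

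Several stronger readings are tempting but not supported:

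- *The plan expects the intervention to change activity.* The article sets out to determine whether it does.
- *A spurious interaction could never be recognised.* The planned model of AAP by arm and a re-run on baseline AAP would give partial checks.
- *This subgroup decides who gets the advice.* No recommendation is tied to it.
- *Leaving the outdoor AAP items unnamed is a defect.* None of the four listed domains is outdoor activity, but item scoring is commonly left to a fuller document.

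It could also be said that baseline was meant. The contrast with (i) and (ii) in the same sentence tells against that, and if it was meant, the same edit is needed.

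**Conclusion.** The point holds as a matter of validity. As worded, subgroup (iii) conditions on a post-randomisation variable that falls can lower and the intervention may change, and it leaves out anyone without a 12-month AAP. Nothing elsewhere in the article cures this.

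The size of the bias cannot be derived from the article. With no true modification and a true ratio of 0.77, it runs from near-nominal error (about 6%, ratios 0.78 to 0.82) to about 20 to 40% false interactions under moderate assumed departures. The still higher rates rest on wider assumed gaps between arms. A reader might infer that the planned test is shown to mislead in a fifth or more of trials; the documents do not support that, because the inputs that produce those rates are assumptions.

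The primary intention-to-treat analysis, the sample size and the other two subgroup analyses are untouched. Severity is moderate.

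**What to change.** In the Statistical analysis section, define subgroup (iii) by AAP outdoor activity at baseline instead of during the trial. If an analysis by 12-month activity is still wanted, for instance to describe exposure to outdoor walking, label it exploratory and non-randomised, and do not report its rate ratios as subgroup treatment effects.

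The cost is one phrase and one sentence. The baseline AAP is already recorded before randomisation, so no new data or visits are needed, and nobody drops out of this analysis for want of a 12-month form.
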